## Sample size and study population

The fundamental rationale relies on the limited capacity theory of attention, positing that highly immersive multisensory environments exhaust finite cognitive resources to mitigate acute pain perception [7]. Furthermore, as demonstrated by Lier et al., virtual reality yields significant overall analgesic efficacy (SMD = −0.65), with particularly robust effects observed among younger demographics [8]. Consequently, the trial enrollment focuses on 60 patients aged 16 to 40 years. Eligible procedures include cardiac and specific thoracic surgeries, such as pulmonary decortication, video-assisted thoracoscopic surgery (VATS), lung biopsy, and Nuss bar pectus excavatum repair.

As this trial is designed as an early-stage, proof-of-concept efficacy study in the specific context of cardiac surgery, a formal a priori power calculation for clinical efficacy is not performed. Instead, a pragmatic sample size of 20 patients per arm (total N = 60) is established. This sample size is aligned with phase IIa / proof-of-concept trials aimed at detecting large clinical effect sizes, evaluating the safety profile of the intervention, and providing initial estimates of variance (mean and standard deviation) to adequately power future, large-scale definitive multicenter trials.

While previous studies have demonstrated substantial effect sizes for VR analgesia in other surgical contexts, extrapolating those parameters to a three-arm, highly invasive cardiothoracic population is not methodologically sound for an a priori power calculation. Therefore, this sample size of 60 serves as a pragmatic and methodologically sound approach. It is sufficiently large to evaluate our primary feasibility metrics and safety profiles, while providing exploratory signals regarding the cumulative opioid consumption to inform future research.

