Conversely, the exclusion criteria are systematically applied and scientifically justified to ensure patient safety and protocol fidelity:•**Clinical and Operational Status:** Patients currently requiring invasive mechanical ventilation at the time of the scheduled intervention (due to physical interference with the VR headset and inability to interact), or those presenting with active infectious-contagious diseases. Recent surgical trials dictate that these exclusions are critical, as such clinical states limit the required active cooperation, pose risks of device displacement, and significantly increase the likelihood of cross-contamination with head-mounted displays [18].•**Cognitive and Neurological Baseline:** Patients with a documented cognitive deficiency, defined by a Mini-Mental State Examination (MMSE) score of 24 or lower, as well as those diagnosed with other cognitive disorders or spatial orientation deficiency. This specific cutoff is supported by Cochrane systematic reviews, which demonstrate that an MMSE score of 24 provides an optimal balance of 85% sensitivity and 90% specificity for detecting cognitive impairment, thereby preventing the inclusion of individuals unable to fully comprehend instructions or interact with complex virtual environments [19].•**Physical and Sensory Constraints:** Individuals with sensory or physical limitations, specifically severe visual impairments and upper limb motor deficits. This exclusion guarantees that patients possess the physical ability to safely interact with the hardware and fully perceive the virtual environment.•**Psychological and Vestibular Intolerance:** Conditions that directly contraindicate immersive technologies, notably claustrophobia and motion sickness, including labyrinthine diseases. While recent meta-analyses confirm that virtual reality is generally safe, mild adverse events such as nausea, dizziness, and cybersickness are still reported, with some clinical trials noting dropout rates of up to 13% due to these symptoms, making the exclusion of highly susceptible populations essential to guarantee patient safety and maintain strict protocol adherence [20].

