## Trial procedures and data collection

The protocol begins in the preoperative phase with a systematic cognitive screening applied to all potential participants. Specifically, the Mini-Mental State Examination (MMSE) is administered to every patient prior to surgery, including those subsequently randomized to the control group, to ensure a baseline of cognitive function that is homogeneous across the entire cohort. Furthermore, once clinically stabilized after surgery and extubated in the ICU, randomized patients start their assigned VR sessions from the first to the fifth postoperative day. The target duration for each session is 45 min to maximize the immersive analgesic effect. However, to prioritize patient comfort and mitigate visual fatigue, the protocol permits a voluntary early cessation at 30 min based on spontaneous patient requests, thereby defining the 30 to 45 min therapeutic window. These sessions are performed three times daily. The total cumulative time of hardware exposure is recorded for each participant to ensure a standardized evaluation of the immersive therapeutic dose across all intervention groups. Specifically, this therapeutic dose will be analyzed as a continuous variable, calculated by summing the total minutes across all 15 sessions. Early interruptions are not classified as protocol deviations, but rather as expected natural fluctuations in patient tolerance, being appropriately captured as a lower cumulative dose within the Intention-to-Treat (ITT) framework.

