Alongside these daily clinical assessments, the safety and tolerability of the intervention are continuously evaluated. Hemodynamic and respiratory parameters, comprising heart rate, mean arterial pressure, oxygen saturation, and respiratory rate, are recorded immediately before and after each virtual reality session. The research team actively monitors for signs of cybersickness, such as nausea or dizziness, as well as physical adverse events ranging from neck pain to skin lesions caused by the headset. Consequently, safety and hygiene protocols, which have been approved by the Hospital Infection Control Committee (CCIH), are paramount for trial replication. The equipment undergoes a cleaning process involving the disinfection of the headset's external hard plastic surfaces with 70 percent isopropyl alcohol wipes. To preserve structural integrity and prevent degradation of the anti-reflective coatings, the VR optical lenses and the auxiliary mirroring tablet screens are cleaned using a specific non-alcoholic optical screen cleaning solution (Implastec, Brazil) applied with dry microfiber cloths. To prevent cross-contamination, patients are provided with specific disposable ocular masks designed for virtual reality headsets. Furthermore, the head straps are wrapped in a protective plastic film that is replaced between each patient use. Throughout the process, the protocol allows for immediate cessation of the session if any discomfort arises. Moreover, in the unlikely event of a serious or unanticipated adverse reaction, the research team is mandated to halt the intervention immediately, provide appropriate medical care, and report the incident to the Institutional Review Board within 24 h, in compliance with ethical guidelines.

Furthermore, broader secondary clinical trajectories and major postoperative complications are monitored to provide a comprehensive recovery profile. The study tracks the length of stay in both the intensive care unit (ICU) and the hospital, the total cumulative duration of mechanical or noninvasive ventilation required throughout the ICU stay, and the incidence of critical events such as delirium, assessed via the CAM ICU protocol, or paralytic ileus.

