To preserve the integrity of the initial randomization sequence while avoiding the imputation of an entire evaluation period for early dropouts, the primary efficacy analysis will be conducted adhering to a modified Intention-to-Treat (mITT) principle. This approach encompasses all randomized participants who received the allocated intervention and underwent at least one post-randomization clinical assessment. To handle potential missing longitudinal data resulting from early clinical discharge, severe postoperative complications, or protocol non-adherence, the analysis will rely on the inherent capacity of the GLMM to manage missing observations under the Missing at Random (MAR) assumption. Additionally, to account for data that may be Missing Not at Random (MNAR)—particularly due to asymmetric dropout rates driven by intervention-related adverse effects such as cybersickness—a sensitivity analysis utilizing Pattern-Mixture Models will be conducted to assess the robustness of the primary findings. Furthermore, a secondary per-protocol analysis will be performed for participants who completed a minimum of two therapeutic sessions per day to evaluate the intervention’s efficacy under optimal adherence conditions. A standard significance level of p < 0.05 will be established. Finally, the statistician performing the final data analysis will be blinded to the group allocation codes.

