Moreover, the implementation of this protocol relies on a stable technological infrastructure. As identified during pilot assessments, hospital wireless network blind spots can disrupt the delivery of streaming content, necessitating the use of pre-downloaded offline media as a mandatory contingency for the passive therapy arm. Parallel to these technological barriers, language can act as an immersion limiting factor. Since the primary interactive applications utilized, such as First Hand and Oculus First Contact, feature English interfaces and audio, non-fluent patients might experience a reduced sense of presence. The risk of cybersickness, although minimized by the careful selection of appropriate software, also remains a physiological factor that could lead to the premature cessation of sessions in highly susceptible individuals.

Because the protocol strategically focuses on a specific age group of 16 to 40 years to ensure technological familiarity, the results may not be directly generalizable to older populations, who might face completely different cognitive or physical challenges when interacting with VR technology. Ultimately, as a single center trial conducted within a highly specialized academic institution, the findings may have limited external validity when extrapolated to community hospitals with different resource constraints. Furthermore, the study design restricts the evaluation window to the acute perioperative phase, concluding on the fifth postoperative day or at hospital discharge. This timeframe inherently limits the ability to assess the long term impact of the VR intervention on the prevention of chronic postsurgical pain or prolonged opioid dependence.

Finally, as a proof-of-concept trial, this study has inherent statistical limitations. The pragmatic sample size of 20 patients per arm (N = 60 total) is prospectively established without a population-specific a priori power calculation. Consequently, while this sample size is mathematically adequate to detect large clinical effect sizes and provide initial estimates of variance, the study may be underpowered to identify small-to-moderate differences in cumulative opioid consumption or pain intensity. Therefore, the risk of a Type II error cannot be completely ruled out, and these findings should be interpreted as preliminary efficacy signals that require validation in future, fully powered definitive multicenter trials.

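### The ventilation outcome counts all invasive ventilation before first extubation, which VR cannot affect, so any VR effect on it is diluted

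*Protocol article*

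**What the plan says.** The outcome stands under Clinical endpoints and blinding, where "broader secondary clinical trajectories and major postoperative complications are monitored to provide a comprehensive recovery profile". Among the items tracked is "the total cumulative duration of mechanical or noninvasive ventilation required throughout the ICU stay". The window is thus fixed as the whole ICU stay, and both kinds of ventilation count.

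Two other sections fix when VR can act. Under Trial procedures and data collection, "once clinically stabilized after surgery and extubated in the ICU, randomized patients start their assigned VR sessions from the first to the fifth postoperative day". Exclusion criteria under Sample size and study population bar "Patients currently requiring invasive mechanical ventilation at the time of the scheduled intervention".

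On size, "a pragmatic sample size of 20 patients per arm (total N = 60) is established", and "a formal a priori power calculation for clinical efficacy is not performed". The statistical section assigns the mixed model, with surgical type as a covariate, to the primary outcome and the longitudinal secondary outcomes, specifically the repeated pain scores. For cross-sectional continuous data it names one-way ANOVA or Kruskal-Wallis. On significance, "A standard significance level of p < 0.05 will be established".

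**The concern.** An outcome used to compare arms should be measured over time in which the arms can differ because of treatment. Here the clock runs from before the treatment can start. For a patient extubated once and never ventilated again, all of the recorded time precedes VR.

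The population makes this more than a formality. Eligible operations run from valve and aortic surgery to VATS, lung biopsy and Nuss repair. The randomisation section describes fixed blocks of three and names no surgical stratum. Initial ventilation may therefore vary widely for reasons unrelated to VR, and on the stated plan a cross-sectional outcome such as this one is not adjusted for surgical type.

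Two things are at stake. A real effect on later respiratory support may be hidden. And a chance difference in initial ventilation may appear in the recovery profile beside the VR arms, although VR could not have caused it. The trial is also meant to supply variance estimates for later trials, and a variance that includes pre-treatment time would be a poor planning figure for this outcome.

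**Working it through.** The protocol gives no power, event or duration figure for this outcome, so there is nothing to reproduce. The check is first of timing and then, as an illustration, of dilution.

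**Timing**

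| Segment of ventilation | Counted? | Can VR have preceded it? |
|---|---|---|
| Invasive, up to first extubation | Yes (whole ICU stay) | No (sessions start only after extubation) |
| Noninvasive, after VR starts | Yes | Yes |
| Invasive after re-intubation, once VR has started | Yes | Yes |

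The first row follows from the protocol's own rules and needs no assumption. The last two rows show that the outcome is diluted, not inert.

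**Dilution of power (illustrative)**

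Inputs: 20 per arm (protocol); two-sided alpha 0.05 (the level is the protocol's, the two sides are assumed); one pairwise comparison; normal approximation. Let f be the share of the variance of total ventilation time that arises after VR starts, with the parts before and after independent. The documents do not give f, so a range is shown.

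Detectable difference at 80% power on the post-start part alone:
(1.960 + 0.842) × √(2/20) = 0.886 SD.

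The same effect on the whole-stay total, in SD units of the total, is 0.886 × √f:

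| f | Effect on total (SD) | Power |
|---|---|---|
| 1.00 | 0.886 | 80% |
| 0.75 | 0.767 | 68% |
| 0.50 | 0.626 | 51% |
| 0.25 | 0.443 | 29% |
| 0.10 | 0.280 | 14% |

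**Dilution of the mean (illustrative)**

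If post-start time is a share s of mean total time, a 30% cut in post-start time shows as 30% × s of the total: 22.5% at s = 0.75, 15% at 0.50, 7.5% at 0.25 and 3% at 0.10.

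**Can one outlier create a finding?**

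Assume 19 patients in one arm ventilated for 8 h and one for 72 h, against two arms of 20 all at 8 h.
- Arm mean: (19 × 8 + 72)/20 = 11.2 h against 8.0 h, a rise of 40%.
- Kruskal-Wallis with tie correction: H = 2.00 on 2 df, p = exp(−1) = 0.37.
- One-way ANOVA: F = 1.00 on 2 and 57 df, p = 0.37.

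With an assumed SD of 2 h around 8 h and one 72 h patient, 5,000 simulated trials gave p < 0.05 in 4.7% with Kruskal-Wallis and in none with ANOVA. One outlier moves a reported mean visibly but does not produce a significant result under the planned tests.

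**The case against.** The strongest reply is that no claim of efficacy rests on this item. It is one of several measures of the clinical course in a proof-of-concept trial, opioid consumption is primary, and nowhere does the protocol hypothesise that VR shortens ventilation. Describing the whole postoperative course is a legitimate aim, and a whole-stay total serves it. This stands, and it limits the weight of the point. It does not rescue the total as a between-arm comparison.

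Second, randomisation balances pre-VR time in expectation, and the tests keep their nominal error rate. This also stands. The harm is chiefly lost sensitivity, not bias.

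A reader might infer several stronger things that the documents do not support:
- **Most of the measured time precedes VR.** This is plausible, but no ventilation duration or split before and after VR is given.
- **The outcome cannot respond at all.** Later noninvasive support and re-intubation are counted and can respond.
- **A single long-ventilated patient would create a VR effect.** The check above gives p = 0.37 under either planned test.
- **The follow-up windows conflict.** The Limitations section says "the study design restricts the evaluation window to the acute perioperative phase, concluding on the fifth postoperative day or at hospital discharge", whereas whole ICU and hospital stays can run past day 5. That sentence explains why chronic pain and long-term dependence are not studied. It allows discharge as an end point and does not say that stay records are cut at day 5.
- **Delirium is mis-scored.** How delirium that begins before the first session is handled is detail an article commonly leaves to the full plan.

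A further fair objection concerns the remedy. Restarting every clock when the patient first meets the session criteria would use an event that may follow randomisation, in an ICU whose clinical team is unblinded, and would drop patients who never qualify. The fix below avoids that.

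**Conclusion.** The point holds in a limited form. By the protocol's own timing rules, all ventilation before first extubation is counted in an outcome on which it cannot carry a VR effect. This is a definition the article states and fixes badly, not a missing detail. The consequence is dilution and, at 20 per arm with mixed surgery, room for a chance imbalance to be read as a recovery effect.

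The size cannot be fixed from the documents. Power falls from 80% to between 68% and 14% as f goes from 0.75 to 0.10, assuming independent parts, a normal approximation and an effect confined to post-start ventilation. The point concerns one secondary outcome and leaves the primary analysis untouched. ICU and hospital stay also contain time before VR, but less completely, and need no change on this ground.

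**What to change.** Split the ventilation outcome at first extubation, in the same way in all three arms.

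1. **Between-arm recovery outcome:** re-intubation (yes/no), and hours of noninvasive or repeat invasive ventilation after first extubation.
2. **Population:** all randomised patients, with those never extubated counted and reported by arm. This matters because the modified intention-to-treat definition requires receipt of the allocated intervention. If it were carried over to this outcome, a VR patient never extubated would drop out while a comparable control, who receives standard care, would stay in.
3. **Initial ventilation hours:** report separately by arm as a pre-intervention descriptor.
4. **Whole-stay total:** may be kept as a descriptive figure, stated not to be attributable to VR.
5. **ICU and hospital length of stay:** leave on their existing clock.

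First extubation is preferable to first session as the split because controls have no sessions. Some support between extubation and the first session will still be counted, but under the same rule in every arm.

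The cost is a redefinition of one secondary outcome. Extubation and ventilation times should be in the electronic health record from which data are already extracted, and no clinical management changes. The downside is that events after extubation will be few, so the outcome should be presented descriptively.

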## Statistical analysis plan

The statistical analysis plan will be executed using SPSS software. Initially, continuous variables will be checked for normal distribution using the Shapiro-Wilk test. To compare baseline characteristics and cross-sectional continuous data among the three distinct groups, a One-Way ANOVA or Kruskal-Wallis test will be utilized, as appropriate. Furthermore, categorical baseline outcomes will be assessed through Chi-squared or Fisher's exact tests.

To account for unequal observation windows arising from early hospital discharge or varying ICU lengths of stay, the primary endpoint will be time-standardized. The absolute cumulative opioid consumption will be divided by the individual patient's exact observation time, yielding a standardized rate of Morphine Milligram Equivalents (MME) per 24 h. This primary outcome, along with the longitudinal secondary clinical outcomes (specifically the repeated Visual Analogue Scale scores evaluated at multiple time points), will be analyzed exclusively using Generalized Linear Mixed Models (GLMM). This advanced modeling accounts for intra-subject correlation over time. Crucially, to adjust for the inherent clinical heterogeneity between distinct surgical profiles (e.g., median sternotomy versus thoracic procedures like VATS or Nuss repair), the 'Surgical Type' will be included as a fixed-effect covariate in the model.

To preserve the integrity of the initial randomization sequence while avoiding the imputation of an entire evaluation period for early dropouts, the primary efficacy analysis will be conducted adhering to a modified Intention-to-Treat (mITT) principle. This approach encompasses all randomized participants who received the allocated intervention and underwent at least one post-randomization clinical assessment. To handle potential missing longitudinal data resulting from early clinical discharge, severe postoperative complications, or protocol non-adherence, the analysis will rely on the inherent capacity of the GLMM to manage missing observations under the Missing at Random (MAR) assumption. Additionally, to account for data that may be Missing Not at Random (MNAR)—particularly due to asymmetric dropout rates driven by intervention-related adverse effects such as cybersickness—a sensitivity analysis utilizing Pattern-Mixture Models will be conducted to assess the robustness of the primary findings. Furthermore, a secondary per-protocol analysis will be performed for participants who completed a minimum of two therapeutic sessions per day to evaluate the intervention’s efficacy under optimal adherence conditions. A standard significance level of p < 0.05 will be established. Finally, the statistician performing the final data analysis will be blinded to the group allocation codes.

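### Length of stay and the other single-measure continuous outcomes are, by elimination, tested without the Surgical Type covariate, which costs precision

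*Protocol article*

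**What the plan says.** The Statistical analysis plan section of the protocol article describes two routes.

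- **Route A.** At the outset, "continuous variables will be checked for normal distribution using the Shapiro-Wilk test". Then, to compare the three arms on baseline variables and on continuous data measured cross-sectionally, "a One-Way ANOVA or Kruskal-Wallis test will be utilized, as appropriate".
- **Route B.** The time-standardised opioid rate and the longitudinal secondary outcomes go to a generalized linear mixed model. The only longitudinal outcome named is repeated VAS. The section continues: "Crucially, to adjust for the inherent clinical heterogeneity between distinct surgical profiles", giving sternotomy against VATS or Nuss repair as the example, and Surgical Type "will be included as a fixed-effect covariate in the model".

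The section *Clinical endpoints and blinding* lists further continuous secondary outcomes: "the length of stay in both the intensive care unit (ICU) and the hospital", the cumulative duration of ventilation, and PSQ-18, which is given once, on day 5 or before discharge. The section *Study design and randomization* describes a single sequence of twenty blocks of three, with envelopes numbered 1 to 60 and no stratification by surgery.

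**The concern.** The plan adjusts for surgery because the operations differ, yet the covariate appears in only one of its two routes. The eligible operations run from valve and aortic surgery to lung biopsy. Length of stay could depend on the operation at least as much as pain does. The section *Sample size and study population* in fact argues that pain is comparable across these operations, and makes no such argument for recovery time. Since randomisation is not described as stratified, the analysis is the only place left to deal with surgery mix.

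At stake is how precisely a trial of 20 patients per arm can estimate effects on recovery. The same section justifies the sample size partly by the variance estimates it will supply for later trials. An unadjusted variance for stay would include the spread between operations, and a Kruskal-Wallis test gives no effect estimate to carry forward.

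**Working it through.** **1. Which outcome goes where.** The article states no power figure to reproduce, so the first step is to match outcomes to methods.

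| Outcome | Values per patient | Route that fits | Surgical Type in analysis |
|---|---|---|---|
| Opioid rate | named in route B | B | yes |
| VAS | repeated | B | yes |
| ICU stay, hospital stay | one | A | no |
| Ventilation time | one | A | no |
| PSQ-18 | one | A | no |

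Route A names cross-sectional data separately from baseline characteristics, so it is not confined to the baseline table. The last three rows are assigned by elimination, because the analysis section does not name these outcomes.

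**2. Size of the precision loss, in closed form.** From the article: 20 × 3 = 60 patients, 20 per arm, significance level 0.05. Assumed, because the article gives none of it: half the patients cardiac, log-normal stay, cardiac stay *r* times thoracic, within-surgery log SD *s*. The share of log variance due to surgery is

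R² = [(ln r)²/4] / [(ln r)²/4 + s²]

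and an unadjusted analysis on the log scale works roughly as if it had 60 × (1 − R²) patients.

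- r = 1.5, s = 0.35: 0.0411/(0.0411 + 0.1225) = 0.25, about 45 patients
- r = 1.5, s = 0.50: 0.0411/(0.0411 + 0.25) = 0.14, about 51
- r = 2.0, s = 0.35: 0.1201/(0.1201 + 0.1225) = 0.50, about 30
- r = 2.0, s = 0.50: 0.1201/(0.1201 + 0.25) = 0.32, about 41

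**3. Simulated power.** Same assumptions, with stay 30% shorter in both VR arms; 3,000 trials per scenario.

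| r, s | Planned two-stage test | Log model, unadjusted | Log model + Surgical Type |
|---|---|---|---|
| 1.5, 0.35 | 79% | 82% | 92% |
| 1.5, 0.50 | 52% | 54% | 60% |
| 2.0, 0.35 | 59% | 63% | 92% |
| 2.0, 0.50 | 42% | 46% | 61% |

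The log scale accounts for 2 to 4 points and adjustment for the rest. Repeat runs put the overall ranges at 41-81% planned and 58-92% adjusted.

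A separate set (4,000 trials per scenario, log SD 0.5, a shift of 0.8 residual SD in both VR arms) varied R² directly:

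| R² | Planned | Adjusted | Gap |
|---|---|---|---|
| 0 | 70.0% | 72.9% | 2.9 points |
| 0.10 | 64.3% | 71.5% | 7.2 points |
| 0.30 | 51.5% | 72.1% | 20.6 points |
| 0.50 | 37.0% | 71.0% | 34.0 points |

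The gap at R² = 0 comes from the form of the test, not from adjustment.

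**4. Type I error.** With surgery mix left to chance, the planned two-stage test rejected a true null in 4.6-5.2% of trials. In the second set, Shapiro-Wilk failed to reject normality in at most about 4% of trials, so the rule nearly always ends in Kruskal-Wallis.

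**5. Chance imbalance.** Suppose the arms hold 13, 7 and 10 cardiac patients. With no VR effect, the expected log difference between the first two arms is (13 − 7)/20 × ln r. That is 0.3 × 0.405 = 0.12 for r = 1.5 (ratio 1.13) and 0.3 × 0.693 = 0.21 for r = 2 (ratio 1.23). Given that split, null rejection was roughly 6-9% as planned and 4.2-5.7% adjusted. A gap of six or more cardiac patients between some two arms arises in about 19% of trials.

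**The case against.** Several points on the other side carry weight.

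- **The routing is inferred.** The paragraph is largely about baseline comparison, and a fuller analysis plan may assign these outcomes elsewhere. That stands as a caveat. But the article does fix a method for cross-sectional continuous data, and no other stated method fits these outcomes.
- **The plan never says that stay needs adjustment.** A reader might infer that it drops an adjustment it has itself declared necessary for these outcomes. The text does not support that: the sentence on heterogeneity is written for the mixed model. Only the reason given there carries over.
- **The unadjusted test is valid.** A reader might infer that chance imbalance makes it produce false differences. Averaged over randomisation it does not. The 6-9% applies only given a lopsided split, and is balanced by lower error in other allocations.
- **Surgery does not drown every effect.** The planned test keeps about 41-81% power in the scenarios examined, and every input to them is assumed.
- **The outcomes differ.** Sessions start only after extubation, so initial mechanical ventilation precedes VR and precision matters less for it. Nothing in the article shows that PSQ-18 depends on surgery. The argument is mainly about length of stay.
- **These are secondary outcomes** in a proof-of-concept trial that does no power calculation and admits a risk of type II error.

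These points lower the priority. They do not remove the gain from using a covariate that the trial already records.

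**Conclusion.** The point holds as one of consistency and efficiency. As written, the single-measure continuous secondary outcomes are analysed without Surgical Type, and the plan's own reason for adjusting extends to length of stay. There is no bias and no inflation of type I error on average, and the normality pretest itself does little harm. The cost is precision, plus exposure to chance imbalance that the described randomisation does not control.

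Under the stated assumptions adjustment adds from about 8 points of power (r = 1.5, s = 0.5) to about 33 points (r = 2, s = 0.35). If surgery type is not prognostic, the gain from adjusting is close to nil and so is the penalty. The size therefore depends on the surgery mix and the spread of stay, neither of which the article gives. Priority is minor to moderate.

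**What to change.** State one prespecified analysis for each single-measure continuous outcome, with arm and Surgical Type as terms, Surgical Type coded as in the mixed model, and no Shapiro-Wilk switch:

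- ICU and hospital stay: a model on the log scale or with a log link.
- PSQ-18: a linear model.
- Ventilation time: a method that allows zeros, since a plain logarithm fails there; for example, a rank test stratified by Surgical Type.

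The change is to wording only, and no new data are needed. The cost is one degree of freedom for each Surgical Type level beyond the first. The article does not give the number of levels. Two levels leave 60 − 3 − 1 = 56 residual degrees of freedom. Coding all eight listed procedure types (four cardiac, four thoracic) separately would leave 60 − 3 − 7 = 50, so the coding should be fixed in advance.
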